### Aims of the trial

The primary aim of this study is to investigate the effectiveness of MCT+ versus computerized cognitive remediation (CR; MyBrainTraining^©^) in individuals with psychosis.

The primary research question is:Does MCT+ result in a greater reduction in rater-observed symptoms of delusions, as measured by the Psychotic Symptom Rating Scales (PSYRATS delusions subscale), compared to computerized CR at the end of treatment (6 weeks)?

Secondary research questions are:2)Does MCT+ result in a greater reduction in other positive, negative and affective psychopathology than computerized CR as measured by the Positive and Negative Symptoms Scales (PANSS)?3)Does MCT+ result in a greater reduction in jumping to conclusions than computerized CR? Is change in jumping to conclusions associated with improvement in positive symptoms?4)Does MCT+ result in a greater reduction in self-reported symptoms of depression and/or a greater increase in quality of life, self-esteem, and cognitive insight than computerized CR?5)Does computerized CR result in a greater improvement in neuropsychological functioning than MCT+?6)Are baseline characteristics or therapy motivation predictive of treatment response to MCT+?

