Although small, yet significant, decreases in psychosis symptoms have been reported in some studies of CR interventions [13], based on previous work, we hypothesize that MCT+ will lead to a greater decrease in delusions as compared to patients in the computerized CR group at post and follow-up test sessions (Q1). Cognitive remediation is deemed an appropriate comparison group for the present study since its feasibility has been asserted, and because it offers some amelioration of neuropsychological symptoms, but does not address cognitive biases at the core of MCT+. We further hypothesize that, compared to the control group, we will find a greater reduction in the PANSS positive syndrome [50] at the same time points for MCT+ participants (Q2). Given previous mixed results regarding improvement in jumping to conclusions [30, 51], we hypothesize that data gathering will improve in both groups, but that only improvement in the MCT+ group will be significantly associated with improvement in delusions (Q3). Because the newest version of MCT+ places more focus on affective symptoms and significant (sleeper) effects have already been detected for quality of life and self-esteem in group MCT (which did not include these new therapy units), we anticipate that participants who complete MCT+ will demonstrate improvements in depressive symptoms, quality of life and self-esteem, which are superior to the control group (Q4). As mentioned above, a limited number of previous studies have yielded mixed findings regarding the effects on cognitive insight. Therefore, we do not expect changes in this domain. Trials on CR programs, as well as our own work, suggest that CR exerts a small to moderate effect on neurocognition [47, 52]. Therefore, it is expected that participants in the control group will experience greater improvements in neuropsychological functioning than those in MCT+ (Q5). Finally, we posit that participants with greater therapy motivation will have a better response (i.e., greater decrease in delusions) to MCT+ (Q6). Based on previous MCT trials [53], we hypothesize that participants with symptoms in the moderate range will benefit most from MCT+.

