### Procedure and treatment allocation

Recruitment occurs in different ways: recruitment by study staff during inpatient stays, referrals from mental health professionals at clinics both within the cooperating centers and in the community (including private practices), and by self-selection through advertisements or word-of-mouth, for example, from Internet searches for schizophrenia treatment in the community. Interested patients receive an informational leaflet and undergo a screening interview by telephone or in-person with research assistants to assess eligibility. If patients appear eligible upon initial contact, they are invited for baseline testing in which informed consent is obtained (or it is obtained before testing for patients with guardians for medical decision-making).

Blinded in-person assessments conducted by trained study research assistants, psychologists or psychiatrists are performed at baseline, 6 weeks and 6 months after baseline (see Table 1). All raters complete a rater-training workshop and also receive individual training in which they are observed as the measures are administered. The 6-week intervention phase begins directly after completion of baseline testing. To diagnose or confirm the diagnosis of psychosis or an affective disorder with psychotic features, as well as to rule-out acute suicidality and substance dependence, a semi-structured interview with the M.I.N.I. is completed with all patients at baseline and 6-month sessions. A questionnaire for intervention group preference and motivation is completed at the beginning of the first treatment session. Questionnaires assessing participants’ acceptance of both interventions are completed at post and follow-up. The sociodemographic interview and all other measures, including semi-structured interviews for schizophrenia symptoms (PANSS and PSYRATS), self-report questionnaires, and neuropsychological measures are completed at all three testing sessions (see Table 2 for list of measures and administration time points).

**Table 1 Tab1:** Schedule of enrollment, interventions, and assessments

	Study period				
	Enrollment	Randomization	Intervention (12 bi-weekly sessions)	Post (6 weeks)	Follow-up (6 months)
Timepoint	T-1	T0		T1	T2
Enrollment					
Eligibility screen	X				
Informed consent		X			
Randomization		X			
Interventions					
MCT+			X		
Cognitive Remediation			X		
Assessments					
Baseline		X			
Post-intervention				X	
Follow-up					X

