**Table 2 Tab2:** List 1 of study measures and questionnaires

Instrument	Baseline	6 weeks (post)	6 months (follow-up)
*Diagnostic and Measures of Psychopathology*			
Sociodemographic interview	X	X	X
Mini Neuropsychiatric Interview	X		X
Positive and Negative Syndrome Scale	X	X	X
Psychotic Symptom Rating Scales	X	X	X
Calgary Depression Rating Scale	X	X	X
Personal and Social Performance Scale	X	X	X
Negative Symptom Assessment – 4	X	X	X
*Neurocognitive Measures*			
Trail Making Test A & B	X	X	X
Test d2	X	X	X
German Vocabulary Test (premorbid intelligence)	X		
Rivermead Behavioural Memory Test, Story Recall	X	X	X
*Cognitive biases*			
Fish Test	X	X	X
*Questionnaires*			
Short Form-12	X	X	X
Patient Health Questionnaire	X	X	X
Beck Cognitive Insight Scale	X	X	X
Rosenberg Self-Esteem Scale	X	X	X
Evaluation of the Intervention		X	X

A measure was developed by the authors (BS, FB, SM) to assess therapist adherence to the MCT+ manual. For patients who provide informed consent, therapy sessions are video recorded and psychologists familiar with MCT+ assess adherence. Additionally, questionnaires developed by the authors (SM) assessing participants’ acceptance of both interventions are completed after every training session attended.

Participants are allowed to use antipsychotic medications during the entire study and are not withheld from other psychosocial treatments they might be offered or are currently participating in, including participation in MCT group therapy. Participation in concurrent interventions is recorded at post- and follow-up testing sessions. Participants are allowed to withdraw from intervention or assessment sessions upon request without having to disclose a reason. All participants are compensated with 30€ upon completing of each assessment session.

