#### Statistical analyses

Two sets of statistical analyses will be performed. First, on an intention-to-treat (ITT) basis, which considers all patients with available baseline data. An expectation maximization (EM) algorithm will be used to estimate missing values. The second set of analyses will include only participants with baseline and post and/or follow-up data (per protocol, PP). An ANCOVA model will be conducted with group (MCT+/MyBrainTraining^©^) difference between T0 and T1 as the dependent variable. Both treatment (independent of time) and condition*time interaction effects will be evaluated. Change scores between T0 and T2 for the primary outcome, as well as analyses over both time points (T0 vs. T1 and T0 vs. T2) for secondary endpoints (PANSS syndrome scores, Fish Task, PHQ-9, CDSS, NSA, WHOQOL-BREF, RSE, BCIS, PSP, neuropsychological outcomes), will be tested using analogous models. Baseline performance or symptoms, antipsychotic drugs (% of maximum dosage) and concurrent treatment (e.g., group MCT, individual psychotherapy, and occupational therapy) will be included in the models as covariates to explore possible impacts on treatment outcome. Secondary analyses will be conducted to examine change between T1 vs. T2 for primary and secondary outcomes.

A logistic regression will be used to analyze variables that may identify participant response to MCT+, including severity of baseline psychotic symptoms, level of motivation for treatment, satisfaction with group assignment, baseline depression, and number of sessions completed. Two groups will be defined (criterion: decline of 25 % or more points on the PSYRATS from T0 to T2) and non-responders. No interim analyses will be conducted. In a sensitivity analysis, we will explore the effect of missing values using various imputation methods (best and worst observation carried forward, last observation carried forward, full-informational maximum likelihood).

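### Number of sessions completed accrues after treatment starts, yet is listed beside motivation in the response model, so the motivation coefficient may understate the association research question 6 asks about

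*Protocol article*

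**What the plan says.** Aims of the trial, research question 6, asks: "Are baseline characteristics or therapy motivation predictive of treatment response to MCT"+. The hypothesis in the same section is directional: "participants with greater therapy motivation will have a better response".

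Statistical analyses then states: "A logistic regression will be used to analyze variables that may identify participant response to MCT"+. The variables named are severity of baseline psychotic symptoms, "level of motivation for treatment, satisfaction with group assignment, baseline depression, and number of sessions completed". Response is defined by a "criterion: decline of 25 % or more points on the PSYRATS from T0 to T2".

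On timing, Procedure and treatment allocation states: "A questionnaire for intervention group preference and motivation is completed at the beginning of the first treatment session". The Intervention section sets 12 sessions over 6 weeks, and T2 is the 6-month assessment. The Discussion reports average attendance of 80 % of MCT+ sessions in earlier work.

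**The concern.** The order in time is motivation at the start of session 1, then attendance over 6 weeks, then response at 6 months. Attendance therefore lies between the predictor of interest and the outcome. More motivated patients plausibly attend more, and attending more may improve response. A model containing both variables estimates what motivation adds among patients with equal attendance. Research question 6 asks something else: whether motivation, as known at the outset, predicts response.

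If part of the association runs through attendance, the adjusted coefficient leaves that part out. The trial could then report little or no support for its own motivation hypothesis although motivated patients do respond more often. The sessions coefficient is also hard to interpret, because attendance is not randomised. It combines any effect of dose with whatever else distinguishes patients who keep attending.

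**Working it through.** **The plan's own figure.** The protocol gives no figure for the response model, so the trial sample size is the only one to reproduce. With d = 0.35, two-sided alpha 0.05 and power 0.80, n per group = 2 × (1.960 + 0.842)² / 0.35² = 128.1, so 129. The t-based solution is 129.1, so 130 as stated. Allowing for 20 % dropout, 260 / 0.8 = 325; the stated 328 is 4 × 82. The sample size reproduces and is not affected by this point. With equal allocation there are 164 MCT+ patients, and 164 × 0.8 = 131 with follow-up.

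**Inputs for the response model.** From the protocol: 0 to 12 sessions, with mean attendance 0.80 × 12 = 9.6. Everything else is assumed: the motivation-attendance correlation r, the attendance effect b (log-odds per SD of sessions), the direct motivation effect c (log-odds per SD of motivation), and any unmeasured common cause of attendance and response. Sessions were generated as 9.6 + 2.6 × a standard normal score, rounded and clipped to 0–12. Clipping brings the mean to about 9.4.

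**Formula.** To a first approximation, the log odds ratio for motivation is c + r × b without sessions in the model and c with sessions in it. The difference, r × b, is the part that runs through attendance.

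- No link (r = 0, b = 0.5, c = 0.4): exp(0.40) = 1.49 both ways.
- Weak mediation (r = 0.3, b = 0.4, c = 0.3): exp(0.42) = 1.52 against exp(0.30) = 1.35.
- Partial mediation (r = 0.5, b = 0.8, c = 0.2): exp(0.60) = 1.82 against exp(0.20) = 1.22.
- Full mediation (r = 0.5, b = 0.8, c = 0): exp(0.40) = 1.49 against 1.00.

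**Simulation.** Clipping, and averaging over the variables left out, pull the figures without sessions down somewhat. Power is for a significant positive motivation coefficient at n = 131.

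| Assumed paths | OR without sessions | OR with sessions | Power without | Power with |
|---|---|---|---|---|
| No motivation-attendance link | 1.47 | 1.49 | 56 % | 59 % |
| Weak mediation | 1.49 | 1.35 | 60 % | 35 % |
| Partial mediation | 1.69 | 1.22 | 79 % | 14 % |
| Full mediation | 1.41 | 1.00 | 46 % | 4 % |

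A second set used a session spread of 2.5, c = 0.4 and 0.2 log-odds per session. It gives 1.53 versus 1.49 at r = 0.1 and 1.58 versus 1.48 at r = 0.2. Full mediation at r = 0.5 under other assumed attendance effects gives 1.35 versus 1.00 and 1.33 versus 1.01.

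**Reversal.** An odds ratio clearly below 1 appeared only when an unmeasured variable was made to drive both attendance and response. With full mediation plus such a variable the result is 1.35 versus 0.84. With no true motivation or session effect and such a variable it is 0.98 versus 0.76.

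These models contain motivation with or without sessions. They omit the other three listed predictors, so they show the direction and range of the distortion, not a forecast for this trial.

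**The case against.** **Joint entry is inferred.** The article does not say whether the variables enter together, in blocks or one at a time. Separate single-predictor models would remove the problem. This stands as a limit on certainty. Still, one regression with a list of variables is most naturally read as one model, and the list itself puts a treatment-period variable beside pre-treatment ones.

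**The link to research question 6 is inferred.** The regression is not labelled with that question, its list is wider, and it models a responder split, whereas the hypothesis speaks of a decrease in delusions. This also stands, but no other described analysis matches the question.

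**The aim is prediction, not causation.** A conditional association is a legitimate quantity, and the protocol makes no dose-response claim. That is correct. However, a variable known only after treatment cannot be among the baseline predictors the question names, and conditioning on it changes what the motivation coefficient describes. The abstract's interest in mediating factors does not help, because no mediation analysis or staged entry is described for this question.

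**The loss may be nil.** This stands: with no motivation-attendance link nothing is lost, and at a correlation of 0.1 or 0.2 the loss is small. Under full mediation, power is only 46 % even without sessions, so a non-significant result would be likely under either model.

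**Stronger readings.** A reader might infer that the planned model will reverse the motivation effect, or that the protocol shows attendance to depend on clinical course. The documents support neither. The withdrawal provision says only: "Participants are allowed to withdraw from intervention or assessment sessions upon request without having to disclose a reason". It does not mention worsening, and the Discussion names a different barrier, cognitive difficulty in remembering appointments. A common cause of attendance and response is therefore an assumption.

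**Conclusion.** The point holds with moderate confidence. Read as one model, the planned regression conditions motivation on a variable that arises after it. To the extent that motivation works through attendance, the coefficient understates the association research question 6 asks about.

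The size cannot be fixed from the protocol. It runs from none when the two are uncorrelated, through modest at a correlation of 0.2, to complete cancellation when the correlation is 0.5 and motivation acts only through attendance. Reversal remains conditional on an unmeasured common cause for which the documents give no evidence. The issue concerns one secondary analysis, so it is worth correcting but does not threaten the trial's main conclusion.

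**What to change.** Take number of sessions completed out of the model for research question 6 and keep only variables known before treatment sessions accrue: baseline symptom severity, baseline depression, motivation as recorded at the start of the first session, and satisfaction with assignment provided it is recorded by then. State that these enter one model. Report sessions completed by arm. If its association with response is of interest, fit it in a separate model labelled descriptive and make no dose-response claim from it.

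The cost is a line or two of analysis wording and no new data. The one loss is the sessions coefficient adjusted for the other predictors.

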##### Primary outcome measure

The PSYRATS is a commonly used semi-structured interview that measures quantitative and qualitative aspects of delusions and hallucinations, including preoccupation, conviction and distress. The difference in PSYRATS delusions subscale score from baseline to follow-up serves as the primary outcome parameter. The validity of the PSYRATS has been demonstrated in chronically psychotic patients and it has been shown to have good psychometric properties [56]. Unlike the PANSS, which collapses important aspects of positive symptoms (e.g., delusion conviction and distress), the PSYRATS allows for a multivariate assessment of delusions and, the PSYRATS is highly correlated with the PANSS.

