**Fig. 1 Fig1:**
[figure not shown]
Study flow

Using calculation software PASS 2008 [77] with a conventional alpha level of .05 and a beta-value of .20 for a two-tailed test, it was calculated that each group must be comprised of 130 patients to detect a small to medium effect (*d* = 0.35) at the 6-month follow-up testing. Assuming a dropout rate of 20 % (including dropout due to non-compliance and loss to follow-up), the study will be conducted with a sample size of 328 patients or 82 patients per trial center.

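### The hypothesis that motivation predicts a larger fall in delusions (Q6) is tested only on a 25 % responder cut; a model of the continuous change would usually be more sensitive and costs nothing to add

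*Protocol article*

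**What the plan says.** Four places in the protocol article bear on this.

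- **Aims of the trial.** Q6 asks whether baseline characteristics or motivation predict response to MCT+. The hypothesis that follows explains what better response means: "participants with greater therapy motivation will have a better response (i.e., greater decrease in delusions) to MCT+ (Q6".
- **Primary outcome measure.** The graded quantity is already defined and collected: "The difference in PSYRATS delusions subscale score from baseline to follow-up serves as the primary outcome parameter".
- **Statistical analyses, predictor model.** "A logistic regression will be used to analyze variables that may identify participant response to MCT" (MCT+ is meant). The listed predictors are severity of baseline psychotic symptoms, motivation, satisfaction with the allocation, baseline depression and number of sessions attended. The outcome is binary: "Two groups will be defined (criterion: decline of 25 % or more points on the PSYRATS from T0 to T2) and non-responders".
- **Statistical analyses, continuous models.** The ANCOVA models of change carry baseline performance or symptoms, antipsychotic dose and concurrent treatment as covariates. Motivation is not among them.

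So baseline symptoms appear in a continuous model as well as in the responder model. Motivation appears only in the responder model.

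**The concern.** The hypothesis concerns how much delusions fall. The test asks only whether the fall passes a threshold. Under the cut, a 26 % decline and a complete remission count the same, and so do a 24 % decline and a worsening. Differences within each group, which bear on a hypothesis of degree, do not enter the test.

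The Background section gives the search for characteristics that moderate outcome as one reason for a large trial. The sample is fixed by the primary comparison, so the analysis scale is one of the few things that can still raise or lower the chance of answering Q6. If the cut costs much power, a real association with motivation could be missed and then reported as absent.

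**Working it through.** **1. The plan's own figure.** The Sample size section works "with a conventional alpha level of .05 and a beta-value of .20 for a two-tailed test", "to detect a small to medium effect (*d* = 0.35) at the 6-month follow-up testing". The normal approximation gives n = 2 × (1.96 + 0.8416)² / 0.35² = 128.1, so 129 per group. The two-sample t-test gives 129.1, so 130. This agrees with "each group must be comprised of 130 patients", and power at 130 per group is 0.803. With the stated 20 % dropout, 260 / 0.8 = 325, and the plan uses 328 = 4 × 82. The primary sample size therefore reproduces. No power is stated for Q6.

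**2. Patients available for Q6.** The model concerns response to MCT+, so I read it as fitted in that arm: 130 patients with T2 data as planned, or 328 / 2 = 164 if every randomised patient enters with missing values estimated.

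**3. Assumptions.** The documents give neither the correlation r between motivation and change nor the responder rate p. I take r = 0.20 to 0.30 (0.15 as a sensitivity value) and p = 20 % to 50 %. Two-sided alpha is .05.

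**4. Closed form.** For a normal outcome cut at responder rate p, with an additive predictor effect, the efficiency relative to the continuous outcome is φ(z_p)² / [p(1 − p)]. A test with 80 % power on the continuous scale has non-centrality 1.96 + 0.8416 = 2.80. Multiplying this by the square root of the efficiency gives the power after the cut.

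| p | Efficiency | Information lost | 130 patients count as | Power after cut | Loss from 80 % |
|---|---|---|---|---|---|
| 50 % | 0.637 | 36 % | 83 | 61 % | 19 points |
| 30 % | 0.576 | 42 % | 75 | 57 % | 23 points |
| 20 % | 0.490 | 51 % | 64 | 50 % | 30 points |

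**5. Simulation with five predictors.** Linear model of change against logistic Wald test on the cut, n = 130, 1,500 runs per scenario. The Monte Carlo error of one power figure is at most √(0.25 / 1500) = 1.3 points.

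| r | Linear | Logistic, p = 20 % to 50 % | Loss in points |
|---|---|---|---|
| 0.15 | .38 | .21 to .27 | 11 to 17 |
| 0.20 | .61 to .62 | .37 to .44 | 17 to 25 |
| 0.25 | .81 to .83 | .52 to .64 | 19 to 30 |
| 0.30 | .91 to .94 | .65 to .80 | 14 to 27 |

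**6. Simulation with an actual 25 % relative decline.** Baseline as covariate, assumed baseline mean 11 and SD 5, responder rates 36 % to 64 %, r = 0.20 to 0.30. The loss is 12.9 to 21.3 points at n = 130 and 9.9 to 21.3 at n = 164.

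**7. With n = 164.** The five-predictor simulation gives 9.9 to 30.7 points over r = 0.15 to 0.30. A second simulation, with motivation and baseline only and responder rates of 30 % and 50 %, gives 8 to 30. In that second simulation both tests kept close to 5 % error when there was no effect (.053 linear, .048 logistic).

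**8. A different shape of change.** Steps 4 to 7 all assume an additive effect on roughly normal change. Suppose instead that motivation shifts the chance of being a clear responder: responders fall by 40 to 100 %, others change little, and the odds ratio is 1.5, 1.6 or 1.8 per SD (n = 130, 25 % rule, 2,000 runs). Then linear power is .48, .59 and .78 against logistic .57, .67 and .84, so the logistic model is better. With noisier scores (SD 2.5) it is .45, .56 and .72 against .41, .52 and .70, a loss of only 2 to 4 points.

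**The case against.** The strongest reply is that the size of the loss, and even its sign, depends on a shape of change that the documents do not give. This stands: step 8 shows it, and the power figures must be read as conditional.

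Second, Q6 itself speaks of response, and modelling responder status answers that directly. A relative decline is also a different quantity from an absolute change, not just a coarser copy. This stands in part. A reader might infer that the article contradicts itself; it does not go that far. But the hypothesis under Aims glosses better response as a larger decrease, and no analysis of motivation on that scale is described.

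Third, baseline symptoms already enter the continuous models. This stands and narrows the point mainly to motivation. The article also expects patients with moderate symptoms to gain most, which is not a straight-line pattern; a plain linear term for severity would not test that either.

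Fourth, no reason is given for choosing 25 %. A reader might count that as a fault, but a condensed article commonly leaves such a rationale to the full protocol or analysis plan, so nothing here rests on it.

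Finally, Q6 is the last of the secondary questions and no power is claimed for it. This stands and limits the weight.

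**Conclusion.** The point holds as a mismatch of scale between the motivation hypothesis and its only described test. If change is roughly normal and the predictor effect additive, the cut loses about 36 % of the information at 50 % responders and about half at 20 %. At n = 130 and assumed r = 0.20 to 0.30 this costs roughly 13 to 30 points of power; at n = 164, about 8 to 30.

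Three stronger readings are tempting and are not supported:

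- That the loss is at least 13 points everywhere. It is about 11 at r = 0.15 with n = 130 and 50 % responders, and 8 to 10 in some runs at n = 164. It can vanish or reverse under a clearly bimodal response.
- That the cut discards most of the gradient. The loss is about a third to a half over the responder rates considered.
- That the trial's main result is at risk. The primary comparison and its sample size are untouched.

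The documents give no effect size, responder rate or shape of change for Q6, so the figures show what the cut could cost, not what it will cost. This is a worthwhile, low-cost improvement to a secondary analysis.

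**What to change.** In Statistical analyses, make the main Q6 analysis a linear model of the continuous T0-T2 change in the PSYRATS delusions subscale on the listed predictors, adjusted for the baseline delusions score. Keep the logistic regression on the 25 % responder criterion as a supportive analysis; this also covers the case in which response turns out to be clearly bimodal.

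The cost is about one sentence of wording, with no new data or patients. The small downside is that the main Q6 result is then expressed in PSYRATS points per unit of predictor rather than as an odds ratio of response. The odds ratio can still be reported alongside.

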#### Sample size

This is the first trial of MCT+ in which participants are followed for a longer period after completion of treatment. As such, determination of optimal sample size was based on an initial trial of MCT+ [34], which included 48 patients and yielded medium to large effect sizes (ɳ_partial_^2^ = .08 – .13) compared to cognitive remediation (CogPack^©^). In this pilot study, non-compliance rates were low over the 4-week follow-up (4 %) and patients’ acceptance was excellent. Most patients eligible for treatment agreed to participate in the study, although 26 % refused participation. Non-completion rate from a 6-month follow-up of group MCT was 14 % after six months, although the greatest number of participants (10 %) dropped out during the first four weeks of the study (from baseline to the post-treatment follow-up). Based on this previous work, we anticipate a completion rate of 80 % for the primary endpoint (T0-T2). See Fig. 1 for a flow chart of the recruitment and study procedure.

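### For patients who leave before the 6-week visit, the four planned missing-data sensitivity analyses reduce to two scenarios, and neither varies the departure from missing at random by arm

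*Protocol article*

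**What the plan says.** All references are to the protocol article.

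- **Visits.** Under Procedure and treatment allocation, blinded assessments "are performed at baseline, 6 weeks and 6 months after baseline". The same section and Table 2 place the PSYRATS at each of these three visits and at no other time.
- **Primary outcome.** "The difference in PSYRATS delusions subscale score from baseline to follow-up serves as the primary outcome parameter" (Primary outcome measure).
- **Main analysis.** The intention-to-treat set is the one "which considers all patients with available baseline data", so it includes patients with no later score. For these, "An expectation maximization (EM) algorithm will be used to estimate missing values" (Statistical analyses). The second, per-protocol set requires a post or follow-up score, so it leaves out patients who have only a baseline.
- **Sensitivity analyses.** The methods named for missing values are "best and worst observation carried forward, last observation carried forward, full-informational maximum likelihood" (Statistical analyses).
- **Dropout.** The Sample size section plans for 20%. It cites a group MCT trial with 14% non-completion at six months, in which "the greatest number of participants (10 %) dropped out during the first four weeks of the study".
- **Reasons.** "Participants are allowed to withdraw from intervention or assessment sessions upon request without having to disclose a reason" (Procedure and treatment allocation).

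**The concern.** Sensitivity analyses for missing data are useful in so far as they rest on different assumptions about the patients who left. Here four methods are listed, but three give the same value for a patient with only a baseline score, and the fourth repeats the assumption behind the main analysis.

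The protocol itself gives reasons to think dropout may be informative. The Discussion names stigma, poor insight and distrust of care providers as obstacles to retention, and these are plausibly related to delusions, the primary outcome. Reasons for leaving need not be given. The arms also differ in kind: MCT+ is delivered in sessions with a therapist, while the CR exercises are done independently on a computer. Leavers could therefore differ from observed patients in different ways in the two arms. What is at stake is how far the planned set can show whether the MCT+ effect survives such a difference.

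**Working it through.** **1. The plan's own figures.** With d = 0.35, two-sided alpha 0.05 and power 0.80, the normal formula gives n = 2 × (1.960 + 0.842)² / 0.35² = 128.1, so 129 per arm. The t-test version gives 129.1, rounded up to the stated 130. Then 260 / 0.80 = 325, against 328 stated (4 × 82). These figures reproduce and are not disputed.

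**2. What each rule gives.** A lower PSYRATS score is better.

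| Scores available | Best carried forward | Worst carried forward | Last carried forward |
|---|---|---|---|
| T0 only | T0 | T0 | T0 |
| T0 and T1 | smaller of T0, T1 | larger of T0, T1 | T1 |

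In the first row the imputed T0–T2 change is zero under all three rules, in either arm. No assumption is needed beyond reading observation as the patient's own score. In the second row the rules can differ, but they give at most two distinct values.

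**3. EM and FIML.** Both are likelihood methods that normally rely on missing at random. With the same variables and model they target the same estimate and differ mainly in the standard error. This is a property of the methods; the article does not state it.

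**4. How many patients.** Expected dropouts are 0.20 × 328 = 65.6, about 66.
- If 10/14 = 71% of them leave before T1, as in the cited trial: 65.6 × 10/14 = 46.9, about 47.
- If 10% of all patients leave before T1: 0.10 × 328 = 32.8, about 33.

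**5. Size of one untested departure.** Assume 20% dropout in each arm, with MCT+ leavers 0.5 SD worse at T2 than missing at random predicts and CR leavers as predicted. The overstatement by EM and FIML is 0.20 × 0.5 = 0.10 SD, and 0.10 / 0.35 = 29% of the planned effect.

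**6. Where the planned methods fall.** An illustrative simulation used 2,000 trials with 164 patients per arm and ANCOVA on T2 adjusted for baseline. It assumed a correlation of 0.5 between visits, 0.5 SD improvement in both arms, a true d of 0.35 and 20% dropout completely at random. Estimated benefit of MCT+ in SD:

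| Method | All leave before T1 | 10/14 leave before T1 | Half leave before T1 |
|---|---|---|---|
| Last carried forward | 0.280 | 0.306 | 0.314 |
| Best carried forward | 0.280 | 0.300 | 0.305 |
| Worst carried forward | 0.280 | 0.290 | 0.288 |
| Missing at random (EM/FIML) | 0.350 | 0.356 | 0.349 |
| MCT+ leavers shifted 0.5 SD worse | 0.250 | 0.256 | 0.249 |
| MCT+ leavers shifted 1.0 SD worse | 0.150 | 0.157 | 0.150 |

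In every column both shifted scenarios lie outside the range of the planned methods. The three carried-forward rules differ from one another by at most 0.314 − 0.288 = 0.026 SD.

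**The case against.** The strongest reply is that the set is not empty. No change and missing at random are different assumptions. In the simulation they differ by 0.350 − 0.280 = 0.07 SD when all dropout precedes T1, and by 0.05 to 0.07 SD with the 10/14 split. That is 14% to 20% of d = 0.35. A reader might infer that agreement among the planned methods is built in; this gap shows that they can disagree.

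A reader might also infer that no planned method lets leavers do worse than completers. That is not so either. If patients generally improve by 0.5 SD, zero change already places CR leavers 0.5 SD behind completers and MCT+ leavers 0.5 + 0.35 = 0.85 SD behind. The extra 0.35 SD in the MCT+ arm lowers the effect by 0.20 × 0.35 = 0.07 SD. This stands. However, the size of that penalty follows from the observed improvement in each arm. The analyst does not vary it, and it stops at baseline.

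Other points carry weight:

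- The article undertakes only to explore the effect of missing values. It does not claim to bound it, and a full analysis plan may add more. The point here is limited to the methods the article does name.
- FIML has a use: if EM fills in each value once, standard errors are too small, and FIML addresses that.
- The 71% comes from a group MCT trial with a four-week interval to the post visit. The only MCT+ pilot had 4% non-compliance, and the planned 20% includes non-compliance, so not all 66 need lack scores.
- If best and worst were meant as extremes of the scale or sample, the overlap in the first table would disappear, but the text does not say so.

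**Conclusion.** The point holds in a limited form. For patients with only a baseline score, the four named methods give two scenarios: no change, or missing at random. Neither lets these patients end worse than baseline, and neither varies the departure from missing at random separately in each arm.

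The group affected is about 33 to 47 of some 66 expected dropouts, provided the cited group MCT pattern carries over; 47 is the upper end of that range. The 0.10 SD overstatement (29% of d = 0.35) depends on the assumed 0.5 SD shift in MCT+ leavers at 20% dropout. It is an illustration; the documents do not predict a shift of any size.

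A reader might go on to infer that carrying baseline forward will favour MCT+ because the control arm loses more patients. The documents give no dropout rate by arm and no rate of general improvement, and the Discussion says the control was chosen to maximise completion, so this is not supported.

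The primary estimate and the sample size are unaffected. The weakness lies in the sensitivity analysis, and correcting it is worthwhile because it is cheap.

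**What to change.** In the Statistical analyses section, add as the main missing-data sensitivity analysis for the T0–T2 change in PSYRATS delusions:

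- Multiple imputation by arm, with a shift delta added to the imputed T2 scores of patients whose T2 score is missing.
- Delta varied separately in each arm, from 0 upward until the conclusion changes. The range should extend beyond 0.5 SD, since the no-change scenario may already imply that much.
- The tipping point reported, meaning the pair of shifts at which the conclusion changes, so that readers can judge whether it is plausible.

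Keep FIML as the missing-at-random reference. Keep one carried-forward analysis as a supplementary no-change scenario.

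The cost is a change of wording and a few hours of programming, with no new data, visits or patients. The downside is a presentation less familiar to some readers than carried-forward results. Recruitment was still under way when the article was submitted, so at that stage the change could be made before any outcome comparison.
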